Recent studies have compared the measurements of these wristbands with those of actigraphy and PSG techniques. PSG involves different types of electrodes (electroencephalogram (EEG), electrooculogram (EOG), electromyogram (EMG), and electrocardiogram (ECG)) to classify the stages of sleep [42]. A few studies have shown that the usability of an ECG signal can determine the stages of sleep [43,44,45,46]. Nevertheless, some have considered the need for further research due to the insufficient quality of this classification compared to the combination of the other electrodes [47,48].

In general, wearable devices can determine the stages of sleep through a heart rate (HR) sensor, which measures the HR, and an accelerometer that detects movement. Previously validated wearable devices have shown a high precision and sensitivity, but also a low specificity and poor agreement in sleep-stage classification when compared with PSG [20,32,33,49,50]. It would be logical to expect these devices to measure sleep more accurately; however, according to these studies, there is a wide range of improvements that can still be accomplished [51,52]. As a result, this protocol has been designed to validate the Xiaomi Mi Smart Band 5 due to its low cost and high acceptance among users, as it is the best-selling fitness tracker [53]. This device has the capability of tracking the activity and HR of users, and classifies the user’s state as being awake or in light sleep, deep sleep, or REM sleep [54].

Therefore, this research focuses on determining whether sleep stages recorded by the new Xiaomi Mi Band 5 can effectively replace PSG sleep-stage classification in sleep-study participants. To this end, the following features will be calculated for both devices: total sleep time, sleep efficiency, sleep latency, and wake after sleep onset. Sleep stages will also be recorded.

Thus, the primary purpose of the present study is to validate the quality of the data generated by Xiaomi wearables when compared with the PSG technique from a hospital sleep unit.

The secondary objectives are: (1) to determine the total sleep time, sleep efficiency, sleep latency, and wake after sleep onset from both the wearable device and PSG; and (2) to examine whether the classification of sleep stages provided by wearable devices is comparable with classifications based on PSG.

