### 2.8. Data Analysis

The analysis will be performed by using the statistical software R. Numeric variables will be expressed as mean (M) and standard deviation (SD), including the range, minima, and maxima. Beyond simple data and study variable descriptions, inferential analysis will be performed in order to determine possible significant relationships between the variables of the study.

A paired-sample Student’s t-test will be used to compare the means of the different sleep parameters of interest. T-test effect sizes are 0.2 (small effect), 0.5 (moderate effect), and 0.8 (large effect), so if the means of two groups do not differ by a 0.2 standard deviation, the difference is trivial, even if there is a statistically significant relationship. [62]. Bland–Altman plots will be used to assess the concordance between both devices for each of the sleep parameters (total sleep time, sleep efficiency, and wake after sleep onset). A positive bias indicates that the device tends to underestimate a variable when compared with PSG. A negative bias indicates that a sleep variable is overestimated [63]. Point estimations will be calculated, as well as their 95% confidence interval.

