An epoch-by-epoch (EBE) (min × min) analysis will be performed in order to calculate the sensitivity (the proportion of epoch segments identified as a sleep state by the PSG that are correctly identified by Xiaomi), specificity (the proportion of epoch segments identified as a waking state by the PSG that are correctly identified by the Xiaomi wristband), and the level of agreement between both devices for light sleep identification (the proportion of PSG-classified N1 + N2 stages identified as light sleep by the Xiaomi wristband), deep sleep identification (the proportion of PSG N3 + N4 stages identified as deep sleep by the Xiaomi wristband), and REM sleep identification (proportion of PSG-classified REM stages identified as REM sleep by the Xiaomi wristband) [64]. Data analysis will include the cleaning or preprocessing, description, and processing of the stored data. The final aim of this workflow will be to obtain useful information that can be used for decision-making. During preprocessing, the wrong values of the dataset will be removed or corrected to avoid bias in the results. Subsequently, obtaining a descriptive statistic study that summarizes relations and distributions in a simple way will help us to know which processing strategy needs to be taken. When processing, information extraction will be performed.

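### The stage agreement figures in section 2.8 are stage sensitivities: read alone, each rises when the band over-calls that stage, so secondary objective 2 is only partly answered

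*Protocol article*

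**What the plan says.** Secondary objective 2, at the end of the Introduction, is "to examine whether the classification of sleep stages provided by wearable devices is comparable with classifications based on PSG". Section 2.8 (Data Analysis) serves it with an epoch-by-epoch comparison. It introduces "the level of agreement between both devices for light sleep identification", with deep and REM sleep following, and defines each figure in brackets:

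- light: "the proportion of PSG-classified N1 + N2 stages identified as light sleep by the Xiaomi wristband"
- deep: "the proportion of PSG N3 + N4 stages identified as deep sleep by the Xiaomi wristband" (Table 1 defines deep sleep as N3 only; that difference is a separate matter)
- REM: "proportion of PSG-classified REM stages identified as REM sleep by the Xiaomi wristband"

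The same sentence defines sensitivity for sleep as a whole, and one specificity, for wake only: "the proportion of epoch segments identified as a waking state by the PSG that are correctly identified by the Xiaomi wristband".

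Two other analyses bear on the point. Bland–Altman plots are planned "for each of the sleep parameters (total sleep time, sleep efficiency, and wake after sleep onset"), so stage minutes are not on that list. The other is the paired test: "A paired-sample Student’s t-test will be used to compare the means of the different sleep parameters of interest". Table 1 lists light, deep and REM minutes among the features of interest, so the test may cover them.

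**The concern.** All three stage figures have the form P(band says stage | PSG says stage). For sleep versus wake, section 2.8 calls this construction sensitivity and pairs it with a specificity. For the stages it calls the construction agreement and gives it no counterpart. The Introduction, when it sums up earlier wearables, treats sensitivity, specificity and stage agreement as separate properties.

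A figure of this form has two gaps. Epochs that the band wrongly gives to a stage do not enter it, so labelling more epochs as that stage can only hold the figure level or raise it. And a band that labels at random scores its own labelling rate, which can look respectable for a stage it calls often.

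The Discussion expects users and health professionals to act on the band's output. They see the band's label, not the PSG stage, so what they need to know is how often that label is right. The planned figures condition the other way round.

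**Working it through.** **The plan's own figure.** The article gives no numerical target for stage agreement. Its one computed figure is the sample size in section 2.5: n = (SD × (z₀.₉₇₅ + z₀.₉₀) / difference)² = (30 × 3.2415 / 15)² = 42.03, rounded up to 43. It reproduces (SD taken as minutes). It concerns mean deep-sleep time and does not depend on how agreement is defined.

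The stage minutes and error rates below are assumptions for illustration; the article gives none.

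**Example 1: over-calling deep sleep.** Assume PSG wake 60, light 220, deep 60, REM 80 min (420 in all). The band labels every epoch correctly, except that it calls 30% of light sleep deep.

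- False deep minutes: 0.30 × 220 = 66. Deep minutes shown: 60 + 66 = 126.
- Section 2.8 deep figure: 60/60 = 100%.
- Positive predictive value (PPV) of a deep label: 60/126 = 47.6%.
- Deep specificity: (360 − 66)/360 = 81.7%.

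**Example 2: chance.** On the same night, a band that assigns light at random to 65% of epochs scores 65% on light sleep. Kappa is 0, and the PPV of its light label is only the share of light sleep in the night, 220/420 = 52.4%.

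**Example 3: over-calling light sleep with an imperfect band.** Assume PSG wake 80, light 240, deep 80, REM 80 min (480 in all). The band has light sensitivity 70% and light specificity 65%; it labels 60% of deep, 60% of REM and 50% of wake correctly. Its totals are wake 56, light 252, deep 92, REM 80 min. Then relabel half of all its non-light calls as light.

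| | Before | After |
|---|---|---|
| Light figure of section 2.8 | 168/240 = 70% | 204/240 = 85% |
| Light specificity | 156/240 = 65% | 78/240 = 32.5% |
| Light PPV | 168/252 = 66.7% | 204/366 = 55.7% |
| Light versus rest: observed agreement | 324/480 = 0.675 | 282/480 = 0.5875 |
| Light versus rest: kappa (expected agreement 0.5) | 0.35 | 0.175 |
| Deep and REM figures of section 2.8 | 60% each | 30% each |
| Wake specificity | 50% | 25% |
| Four stages: observed agreement | 304/480 = 0.633 | 272/480 = 0.567 |
| Four stages: expected agreement | 0.342 | 0.421 |
| Four stages: kappa | 0.44 | 0.25 |

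Kappa is (observed − expected)/(1 − expected). The light figure improves by 15 points while the band gets worse on every overall measure. Over assumed mixes with 200 to 300 light minutes in 480, the light figure always goes from 70% to 85%. Light kappa falls from 0.33–0.35 to 0.15–0.19 and four-stage kappa from 0.41–0.45 to 0.24–0.25.

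**What the other planned outputs would show.** In Example 1, light sensitivity drops to 70% and deep minutes are biased by 66. With the section 2.5 inputs, a paired test would give t = 66/(30/√43) ≈ 14. In Example 2, the wake, deep and REM proportions together sum to only 35%. In Example 3, the deep, REM and wake figures all halve. If instead a band assigned labels at random in the PSG proportions of the Example 1 night, mean bias would be zero and the paired test would see nothing. The stage figures would then be 60/420 = 14% for deep and 80/420 = 19% for REM.

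**The case against.** The best reply is that section 2.8 does not offer one figure alone. It plans the correct-label proportion for all four states, and an epoch carries only one label, so over-calling one stage takes epochs from another and lowers that stage's figure. The deep-sleep example would also be caught by the comparison that the study is sized for: 66 minutes is more than four times the 15 minutes that section 2.5 calls clinically relevant. Pooled PPV can even be worked out afterwards as sensitivity × PSG minutes / band minutes (1.00 × 60/126 = 47.6%), and pooled kappa from the four proportions and both sets of minutes. The bracketed definitions tell a careful reader what each proportion is, and the study calls itself a pilot.

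Most of this stands. A reader might infer that nothing planned can detect over-calling, or that objective 2 cannot be answered at all. The document supports neither. The objective is to examine comparability, and the four proportions with stage minutes do examine it, though incompletely.

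The reply leaves three gaps. The back-calculation is not planned, and it works only if proportions and minutes are pooled over the same epochs. It gives no values per participant and cannot show which stage the misclassified epochs went to. And the paired test compares night totals, which can match when the epochs do not.

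It is also fair to say that kappa should not become the sole criterion. It depends on how common each stage is, and other chance-corrected indices exist.

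**Conclusion.** The point holds in a limited form. What section 2.8 calls agreement on light, deep and REM sleep is stage sensitivity. This follows from the written definitions, not from something left to an unseen analysis plan. Read alone, each figure rewards over-calling of its own stage and takes no account of chance. Read together, the planned outputs would partly expose over-calling. No planned analysis directly reports how often a stage label is right, where errors go, or agreement beyond chance, so secondary objective 2 is answered incompletely.

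The direction follows from the definition. The sizes (100% against a PPV of 48%; 70% rising to 85% while light kappa halves) rest on assumed stage minutes and error rates and do not predict how this band will perform. The defect concerns a secondary objective and does not defeat the study, but it should be corrected before the epochs are analysed.

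**What to change.** In section 2.8:

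1. Keep the three proportions, but call them stage sensitivity.
2. From the same matched epochs, add the 4×4 cross-table of PSG by band (wake, light, deep, REM), stage-specific specificity and PPV, and a chance-corrected index such as Cohen's kappa.
3. Compute these per participant and summarise them across participants. State how a participant is handled when a quantity is undefined, for example PPV when the band never assigns that stage.
4. Say that objective 2 will be interpreted on these results together, not on the sensitivities alone or on kappa alone.

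The cost is a little more analysis and a longer results table, and the figures may look less favourable than the sensitivities alone. No new data are needed, and the sample size of 43 is unaffected.

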### 2.9. Ethics and Dissemination

This study protocol was approved by the A Coruña-Ferrol Research Ethics Committee, under the number 2020/318, on 20 July 2020. In addition, this protocol was registered in Clinical Trials Protocol Registration and Results system on 23 September 2020, available at https://clinicaltrials.gov/ct2/show/NCT04568408. In case any change in the protocol is needed, this will be communicated to the ethics committee with the assigned reference number. These modifications will also be updated in the clinical trials registry.

For each participant, the process of informed consent will be applied. Participants will receive complete verbal and written information about the characteristics of the study and about the implications derived from their participation in it. An information sheet that they can read slowly will be given to each participant, and they will be able to ask any questions they may have. Once it has been ensured that all participants fully understand the information provided, they will decide on whether or not they wish to participate in the study and, if they decide to participate, agree by signing the informed-consent document. The main researcher will maintain the confidentiality of all data collected and the anonymity of each participant. Thus, the Spanish and European Organic Law on the protection of personal data will be respected at all times [65,66]. The data of the participants will be collected, encoded, and preserved until the end of the study. Once the study is finished, each participant’s data will be stored for future studies if they provide consent. The results and conclusions of this study will be disseminated through their publication in influential scientific journals and their presentation at appropriate conferences.

## 3. Discussion

The validation conducted in this study will allow us to evaluate whether the Xiaomi Mi Smart Band 5 is a device that can be used as a health promoter by allowing sleep self-assessment in the general population. Due to its low price, it is fairly accessible to any user who considers that they may be suffering from a sleep disorder that is potentially worsening their health [32]. Hence, if the data generated by the smart band proves to be reliable, any health professional could evaluate at a glance whether the user is suffering from a sleep disorder, and whether it influences their daily life activities [40,67]. The widespread use of these devices could help users to self-assess their sleep and connect with health professionals in the case of bad sleep quality, which would imply a better prognosis and a longer and higher-quality life expectancy. It is important to highlight some limitations and risks in studies focused on the validation of wearables, since firmware updates may modify the sleep-tracking algorithm, and the intra-wearables’ sleep measurements do not perfectly match, even when multiple smart bands worn by the same user are identical.

## 4. Conclusions

This project contributes to the validation of the sleep data obtained through the Xiaomi MiBand 5, making a comparison with the PSG data. Therefore, it is intended to determine whether the sleep parameters (TIB, SOL, WASO, SE, light sleep, deep sleep and REM sleep) are correctly measured through the Xiaomi MiBand 5.

The widespread use of these devices by the current society is not expected to replace the PSG. However, the information obtained by the wristbands about sleep is user-friendly in a domestic context, as this sleep data doesn’t need to be processed as in the case of the PSG. Thus, the use of these devices can help the population to be able to objectively determine whether they have difficulties in their sleep or not, as well as to promote healthy lifestyle habits, and if necessary, seek the advice of a healthcare professional.

## Figures and Tables

**Figure 1 ijerph-18-01106-f001:**
[figure not shown]
The recruitment and assessment process.

**Table 1 ijerph-18-01106-t001:** Summary of the features of interest for our study.

Variable	Description	Dimension
Time in bed (TIB)	Total time the patient is laying down	min
Sleep onset latency (SOL)	Length of time from full wakefulness to sleep	min
Wake after sleep onset (WASO)	Periods of wakefulness after defined sleep onset	min
Sleep efficiency (SE)	Time asleep/TIB × 100	%
Light sleep	N1 + N2 sleep stages	min
Deep sleep	N3 sleep stages	min
Rapid Eye Movement (REM) sleep	-	min

## Data Availability

Once the data collection process is finished and these have been coded, structured, and analyzed, these data will be provided, provided that the Spanish Data Protection Agency consents, to any researcher who contacts the TALIONIS group’s Principal Investigator, [name] ([contact]).
